## Abstract

**Background:**

Black adults who smoke and have HIV experience immense stressors (eg, racial discrimination and HIV stigma) that impede smoking cessation success and perpetuate smoking-related health disparities. These stressors also place Black adults who smoke and have HIV at an increased risk of elevated interoceptive stress (eg, anxiety and uncomfortable bodily sensations) and smoking to manage symptoms. In turn, this population is more likely to smoke to manage interoceptive stress, which contributes to worse HIV-related outcomes in this group. However, no specialized treatment exists to address smoking cessation, interoceptive stress, and HIV management for Black smokers with HIV.

**Objective:**

This study aims to test a culturally adapted and novel mobile intervention that targets combustible cigarette smoking, HIV treatment engagement and adherence, and anxiety sensitivity (a proxy for difficulty and responsivity to interoceptive stress) among Black smokers with HIV (ie, Mobile Anxiety Sensitivity Program for Smoking and HIV [MASP+]). Various culturally tailored components of the app are being evaluated for their ability to help users quit smoking, manage physiological stress, and improve health care management.

**Methods:**

This study is a pilot randomized controlled trial in which Black combustible cigarette smokers with HIV (N=72) are being recruited and randomly assigned to use either (1) the National Cancer Institute’s QuitGuide app or (2) MASP+. Study procedures include a web-based prescreener; active intervention period for 6 weeks; smartphone-based assessments, including daily app-based ecological momentary assessments for 6 weeks (4 ecological momentary assessments each day); a video-based qualitative interview using Zoom Video Communications software at week 6 for participants in all study conditions; and smartphone-based follow-up assessments at 0, 1, 2 (quit date), 3, 4, 5, 6, and 28 weeks postbaseline (26 weeks postquitting date).

**Results:**

Primary outcomes include biochemically verified 7-day point prevalence of abstinence, HIV-related quality of life, use of antiretroviral therapy, and HIV care appointment adherence at 26 weeks postquitting date. Qualitative data are also being collected and assessed to obtain feedback that will guide further tailoring of app content and evaluation of efficacy.

**Conclusions:**

The results of this study will determine whether the MASP+ app serves as a successful aid for combustible cigarette smoking cessation, HIV treatment engagement, and physiological stress outcomes among Black people with HIV infection. If successful, this study will provide evidence for the efficacy of a new means of addressing major mental and physical health difficulties for this high-risk population. If the results are promising, the data from this study will be used to update and tailor the MASP+ app for testing in a fully powered randomized controlled trial that will evaluate its efficacy in real-world behavioral health and social service settings.

**Trial Registration:**

ClinicalTrials.gov NCT05709002; https://clinicaltrials.gov/study/NCT05709002

**International Registered Report Identifier (IRRID):**

PRR1-10.2196/52090

## Introduction

### Background

People with HIV/AIDS smoke at a rate 3 times higher (33.6% vs 12.5%) than that of the general population [1,2]. This group is also less likely to quit smoking and is more susceptible to the harmful effects of smoking (eg, increased risk for cancer and lung disease) [1,3,4], likely due to the combined impact of several social determinants of health, including behavioral risk factors, limited resources, and diminished access to health care, as well as immune system dysfunction and chronic inflammation caused by HIV [5-10]. Indeed, cigarette smoking is a leading risk factor for HIV-related and non–HIV-related morbidity and mortality among people with HIV/AIDS [11,12], even among those taking antiretroviral medications [13], and contributes to more life-years lost than HIV-related complications among those effectively treated with antiretroviral therapy (ART) [13-15]. Furthermore, people with HIV/AIDS who smoke are less adherent to ART than nonsmokers and experience poorer viral and immunologic responses to ART [16,17], a greater risk of virologic rebound, and more frequent immunologic failure [18].

Among people with HIV/AIDS who smoke, those who identify as members of a racial minority group are at an elevated risk for negative health consequences of smoking and poorer HIV-related outcomes. Evidence suggests that Black adults with HIV, in particular, experience high rates of discrimination and stigma that lead to the onset and maintenance of maladaptive coping, including smoking [19,20]. Consistent with these data, Black adults with HIV are more likely to smoke [4], less likely to quit [4,21-24], and experience greater quit difficulty when attempting to quit than White smokers or smokers without HIV [21]. Black adults with HIV also have lower rates of compliance with routine HIV care (ie, ART adherence), retention in long-term care, and are less likely to be virally suppressed relative to other groups [25-28]. This is a public health problem because Black adults account for the highest proportion (42%) of new HIV diagnoses and experience higher mortality than White adults with HIV [25,27,28]. From an intersectional stigma and discrimination perspective and socioecological models of social determinants of health [29,30], Black adults who smoke and have HIV may be at elevated risk for worse HIV disease management and smoking outcomes and ultimately experience increased health disparities [6].

Emotional models of coping suggest that Black adults with HIV may smoke and continue to smoke despite health problems to manage interoceptive stress and uncomfortable physiological arousal associated with minority status stressors such as racial discrimination and HIV-related stigma. Anxiety sensitivity (AS) is one of the most noteworthy constructs related to physiological distress and manifestations of elevated internal distress, including psychopathologies. AS refers to the fear of anxiety or anxiety-related symptoms [31]. AS amplifies negative mood states via enhanced threat perception (eg anxiety) [32,33], contributing to the development of anxiety and depressive problems [34]. Notably, anxiety and depression contribute to an increased likelihood of poor ART adherence [35]. Among people with HIV/AIDS, AS is related to more severe social anxiety symptoms, anxious arousal symptoms, HIV-related stigma, and HIV symptom distress [36,37]. AS has also been implicated as a contributing factor in smoking initiation, maintenance, and relapse [38,39]. Emerging data indicate that AS is elevated in both Black adults who smoke and people with HIV/AIDS who smoke [40], placing this group at greater odds of early lapse and relapse [41,42]. Without appropriate interventions to address susceptibility to the negative impact of interoceptive stress, Black adults with HIV who smoke and have elevated AS may be inclined to return to smoking to alleviate abstinence-induced increases in anxiety and to manage uncomfortable HIV-related bodily symptoms that may increase with smoking cessation.

Although smoking cessation treatments that target AS exist, they are limited in their reach, adaptability, and potential for adoption and do not consider critical barriers to smoking cessation or HIV treatment engagement and adherence. For example, current combined AS and smoking treatments focus primarily on multisession, intensive treatments, particularly those that rely on in-person, clinician-administered psychosocial protocols [43-46]. Participation in these treatments often requires notable time commitments, practical limitations, and expense [47]. Such burdens are barriers to treatment and may contribute to the low treatment participation rates [47]. An additional limitation of current treatments is that no readily available smoking cessation treatments that target AS integrate information to improve HIV treatment engagement and adherence. Given the robust evidence that targeting AS and promoting smoking cessation may lead to improved HIV outcomes, this is a major limitation. Finally, the required human resources, specialized training, and financial support that are needed to administer currently available combined AS and smoking treatments discourage the adoption of these treatments in communities most in need, such as those that serve Black adults with HIV who smoke. Therefore, it is essential to develop a digital AS intervention that can be culturally adapted for this population.

### Objectives

On the basis of our prior work [48], we modified our previously developed and tested novel, integrated, smartphone-delivered intervention for AS reduction and smoking (ie, Mobile Anxiety Sensitivity Program [MASP]) [49] for Black people with HIV/AIDS who smoke, integrating HIV information and care support that is culturally tailored to create the new smartphone-based app: Mobile Anxiety Sensitivity Program for Smoking and HIV (MASP+). MASP+ contains features and content designed to aid Black adults with combustible smoking cessation, HIV care adherence, and AS reduction. The initial efficacy of MASP+ relative to an established control intervention, the National Cancer Institute’s (NCI) QuitGuide app, on combustible cigarette smoking cessation, HIV-related outcomes, and AS reduction is currently being tested in a pilot randomized controlled trial (RCT). We expect that MASP+ participants will report greater biochemically confirmed smoking abstinence at 26 weeks postquitting date relative to the QuitGuide group. In addition, we hypothesize that MASP+ participants will report greater HIV-specific quality of life, ART adherence, and HIV treatment engagement at 26 weeks postquitting date relative to the QuitGuide group. Finally, we expect that improvement in AS will mediate the relationship between treatment and (1) smoking abstinence and (2) HIV-related outcomes and that daily experiences of discrimination (race and HIV) will moderate these relationships. We will also examine qualitative and quantitative data to guide the refinement and further adaptation of MASP+ and support the development of a high-quality, culturally relevant, and scalable intervention.

## Methods

### Ethical Consideration

The Institutional Review Board at the University of Houston (UH) approved the protocol presented in this study under STUDY00003811, whereas the University of Oklahoma Health Sciences Center and Baylor College of Medicine relied on the UH Institutional Review Board. This trial has been registered at ClinicalTrials.gov (NCT05709002; protocol ID: QKWEF8XLMTT3).

### Study Eligibility

The study eligibility criteria included being aged ≥18 years, having HIV, self-identification as Black or African American, providing a current picture of their cigarette package to verify smoking status [48], possessing at least a grade 6 reading level (≥4 on the Rapid Estimate of Adult Literacy in Medicine [REALM]) [50], experiencing elevated AS (ie, Short Scale Anxiety Sensitivity Index [SSASI] score of ≥5) [51], reporting daily smoking with a minimum of 10 cigarettes per day for at least 2 years, being motivated to quit smoking (>5 on a 10-point scale) [52], willingness to complete all study surveys or assessments, agreeing to use nicotine replacement medications (nicotine replacement therapy [NRT]; nicotine patch and lozenges), and agreeing to attempt to quit smoking 2 weeks after the date of randomization. Exclusion criteria included not being fluent in English; high blood pressure that is not under control (eg, medicated); experiencing a heart attack (myocardial infarction) within the past 2 weeks; use of any pharmacotherapy targeting smoking cessation beyond what is provided by this study; legal status that would interfere with participation (eg, incarceration with restricted access to mobile devices); cognitive impairment (assessed via the 6-item Cognitive Impairment Test) [53]; and being non-Black, pregnant, or younger than 18 years.

### Recruitment and Procedures

Participants are recruited via web-based advertisement materials, as well as physical materials placed throughout the city of Houston. Study materials provide contact information for UH if a potential participant has questions about the study. Study advertisements also include a QR code linked to a REDCap (Research Electronic Data Capture; Vanderbilt University) prescreener survey. Those who complete the prescreening are deemed either ineligible or pre-eligible. For those recruited from Thomas Street at Quentin Mease Health Center, a clinic in Houston that provides routine medical care to ≥5000 people with HIV/AIDS study team members at Thomas Street perform a chart review to confirm HIV status. Pre-eligible participants are then contacted to complete an enrollment call wherein they provide informed consent and complete the final eligibility screening for the study (refer to Figure 1 for the participant enrollment flowchart).

**Figure 1 figure1:**
[figure not shown]
Mobile Anxiety Sensitivity Program for Smoking and HIV (MASP+) participant enrollment flowchart. Note: after initial eligibility screening, participants will complete an enrollment call, baseline survey, randomization call, postrandomization survey, 6-week ecological momentary assessment (EMA) period, monthly check-ins for 5 months, and a final survey and week of EMAs at week 28. iCO: iCarbon Monoxide.

Persons deemed eligible at the enrollment call download the Insight app onto their personal smartphone or study phone. The Insight app houses the MASP+ content and is used to administer smartphone-based surveys and ecological momentary assessments (EMAs) to all participants. The study smartphones are provided to those without a smartphone and those with a smartphone that is incompatible with the Insight platform. Insight is supported on most Android smartphones (Android versions 6.0-14.0). Participants with a personal phone that is incompatible with Insight are sent a study phone. For those using their personal smartphone, the study staff instruct participants on how to download the app onto their personal phone. Insight adjusts according to the font size selected by participants on their phones. Participants who experience issues reading text in the app due to font size are instructed to increase font size in the phone settings. Once Insight is downloaded, participants are given a unique single-use code that enables them to use the app to complete the baseline assessment, which must be completed within 6 days after inputting the code. If participants do not complete the baseline survey within 6 days, they are no longer eligible to participate in the study. All participants are mailed a baseline package that includes a Bedfont iCO (iCarbon Monoxide) quit smokerlyzer, a Greenphire Mastercard, and NRT. The Bedfont iCO is used to biochemically verify self-reported abstinence at follow-ups.

Upon completion of the baseline survey and receipt of the baseline package, the participants complete a randomization call with the study staff. During the randomization call, the participants are randomized to receive the MASP+ or QuitGuide interventions based on the randomization chart developed by the study statistician ([name]). Block randomization was used and stratified according to binary sex (assigned at birth). Variable-sized permuted block randomization (block sizes vary from 4 to 12) is used. Before data analyses, the balance of randomization will be checked and controlled for imbalanced factors by including any factors that differ between groups as covariates. The participants are provided with a unique code to access the app to which they are randomized. MASP+ participants have access to all MASP+ features (ie, Treatment Videos, Coping Toolkit, Quit Tips, and Stress Management Trainings) through the Insight platform. Participants randomized to the control intervention (ie, QuitGuide) have access to limited features (ie, App Instructions, Payment Tracking, Call Staff, and Record Stress) through the Insight platform and receive intervention content (ie, Track My Craving, Manage My Mood, and Learn To Quit) through the QuitGuide app. Participants assigned to the control intervention receive assistance with downloading the QuitGuide app through the Google Play Store. Both intervention groups use the Insight app to complete the study assessments, which include the baseline survey, weekly follow-ups, the 28-week follow-up, and EMAs. Once the code is entered, the research staff orients the participant to the app features and the iCO carbon monoxide (CO) breath testing device. Participants have access to MASP+ or QuitGuide content through the final follow-up (ie, the 28-week follow-up). At the end of the randomization call, participants are directed to take a brief postrandomization survey, which must be completed within 6 days after the randomization call. Failure to complete the postrandomization survey within 6 days does not affect participants’ status in the study.

Following randomization, the participants complete 4 daily EMAs for 6 weeks. Participants also complete app-based follow-up surveys each week of the treatment period (ie, weeks 1-6) and at 26 weeks postquitting date (28 weeks postbaseline). Between weeks 6 and 28, all participants are prompted to complete a brief check-in survey each month, which reminds them about available app features and assesses their current smoking status. The participants complete a final series of EMAs (4 per day) for 7 days before the 28-week follow-up assessment. The Insight app prompts daily EMAs and follow-up assessments for both treatment groups. In addition, participants complete a Zoom-based qualitative interview to assess their experience with the app and capture recommendations for improving app features and content at 6 weeks postrandomization. Participants who received loaned study smartphones are required to return them after their final follow-up assessment at week 28.

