### Data Analyses

#### Overview

To test the hypothesis that MASP+ produces higher rates of smoking abstinence compared to the NCI QuitGuide app, a biochemically verified measure of 7-day PPA that is collected during weekly assessments via Bedfont iCO will be used. PPA is defined as no smoking, not even a puff, in the 7 days before follow-up assessments and biochemical verification of smoking abstinence (ie, CO levels <7 ppm according to an iCO test). We will calculate odds ratio effect sizes (with 95% CI) to estimate between-group differences for PPA at each follow-up assessment. The effect size for the comparison between conditions at the 26-week postquitting date assessment will serve as the primary analysis of the impact of treatment condition on smoking cessation.

We will then conduct a series of conditional latent growth curve models (LGM) to examine the impact of treatment condition on abstinence trajectories. First, an LGM will be specified using CO breath tests at 2 (quit date), 3, 4, 5, 6, and 28 weeks. The intercept of these models will be centered on the baseline assessment and will be specified to model linear change across the major assessments. A dummy code representing the treatment condition will be specified as a predictor of the intercept and slope factors to quantify the effect of MASP+ on the longitudinal course of abstinence.

The impact of treatment conditions on HIV quality of life, ART adherence, and HIV treatment engagement (hypothesis 2) will be examined using the same sequence of analyses: between-condition effect sizes followed by conditional LGM. We will then conduct univariate LGM to explore changes in AS a function of treatment (hypothesis 3), followed by a series of parallel process LGM to examine how changes in AS relate to changes in smoking and HIV outcomes. The indirect effects of treatment via AS will be evaluated by calculating bootstrapped CIs of the indirect effect using the MODEL INDIRECT command in MPlus.

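### Covariates are to be chosen by observed baseline imbalance rather than prespecified, which in practice leaves out the stratification factor and gives up precision in the HIV effect-size comparisons

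*Protocol article*

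**What the plan says.** Recruitment and Procedures describes permuted blocks stratified by sex assigned at birth ("block sizes vary from 4 to 12"). It then says that balance will be checked before data analysis and "controlled for imbalanced factors by including any factors that differ between groups as covariates". No candidate factors, test or cut-off are named.

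Data Analyses, Overview, names no covariate. For abstinence: "We will calculate odds ratio effect sizes (with 95% CI) to estimate between-group differences for PPA at each follow-up assessment". For the growth models: "A dummy code representing the treatment condition will be specified as a predictor of the intercept and slope factors". The HIV outcomes follow the same sequence, "between-condition effect sizes followed by conditional LGM". Neither sex nor any baseline value is prespecified as a covariate, so the imbalance rule is the only covariate rule in the article.

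Sample Size Determination says conclusions will rest mainly on effect sizes and their confidence intervals.

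**The concern.** Under randomisation, observed baseline differences arise by chance. A covariate helps when it predicts the outcome, and the size of its chance difference says nothing about that. A rule based on differences therefore admits irrelevant factors that happen to differ and leaves out strong predictors that happen to be balanced. It also makes the analysis model depend on the allocation that occurred. With no list or threshold, the analyst decides what counts as differing.

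The rule also works against the design. Stratifying by sex makes sex balanced, so a rule that looks for imbalance drops the one factor judged important enough to stratify on.

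What is at stake is interval width. In a trial of 72 whose product is effect sizes with confidence intervals, precision available from data already collected is worth having.

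**Working it through.** The plan gives no figure of its own on this point, so there is none to reproduce.

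**Inputs from the article.** N=72; stratification by sex; block sizes 4 to 12; HIV outcomes measured at baseline, week 6 and week 28 (Table 2).

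**Assumed, because the article does not give them.** 36 per arm; outcome SD 1; baseline-outcome correlation r of 0.3, 0.5 or 0.7; 10 candidate factors, of which one (the baseline value) is prognostic; imbalance judged at p<0.05; for the sex check, a 60:40 sex split and even block sizes.

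**1. How often something is flagged.** For k independent factors the chance of at least one flag is 1 − 0.95^k. This is 1 − 0.95^10 = 40% and 1 − 0.95^20 = 64%. Correlated factors would change these values.

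**2. Whether sex is ever flagged.** In 5,000 simulated trials with sex-stratified blocks, sex was flagged in none. The largest difference between arms was about 9 percentage points.

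**3. Precision for a continuous HIV outcome.** The unadjusted standard error is √(2/36) = 0.236. Adjusting for baseline multiplies it by √(1 − r²), giving about 0.225, 0.204 and 0.168. Against no adjustment, the variance reduction is r²: 9%, 25% and 49%. The comparison needed here is with the imbalance rule, which picks up the baseline value in about 5% of trials and also admits irrelevant factors. By simulation:

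| r | Variance reduction, prespecified baseline v. rule | Type I error under the rule |
|---|---|---|
| 0.3 | about 9% | 5.0% |
| 0.5 | about 22% | 4.7% |
| 0.7 | about 43% | 3.6% |

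A separate simulation gave SDs of the effect of 0.236 v. 0.209 at r=0.5, where 1 − (0.209/0.236)² = 22%. At r=0.7 it gave 0.224 v. 0.170, where 1 − (0.170/0.224)² = 42%. A further run of 20,000 trials per setting gave 9%, 21% and 41%, so the figures are good to about two points.

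On the standard-error scale, √0.91, √0.78 and √0.57 are 0.95, 0.88 and 0.75. The empirical standard error is thus about 5%, 12% and 25% smaller with prespecified adjustment.

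**4. With a single candidate factor.** The SDs are 0.233 v. 0.226, 0.228 v. 0.208 and 0.220 v. 0.169, or 6%, 17% and 41% less variance. At d=0.6 (two-sided 5%), power under the rule is 71%, 73% and 73%, against 75%, 82% and 94% with prespecified adjustment.

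**5. Where these figures do not apply.**
- *Abstinence.* Eligibility requires "reporting daily smoking with a minimum of 10 cigarettes per day for at least 2 years", so abstinence has no varying baseline value to adjust for. For an odds ratio, adjusting for a prognostic factor gains power rather than a smaller standard error, because the odds ratio is non-collapsible.
- *HIV and anxiety sensitivity growth models.* The intercept is centred on baseline. The HIV scales have three waves, and a linear growth model on two would not be identified, so the baseline wave is very likely already in the model. Anxiety sensitivity is also measured at baseline and analysed as change.
- *CO growth model.* It starts at the quit date ("an LGM will be specified using CO breath tests at 2 (quit date), 3, 4, 5, 6, and 28 weeks"), so baseline CO is not listed. No precision figure is claimed for it.

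**The case against.** The strongest reply is that this is a condensed article about a pilot and that covariate lists usually sit in the analysis plan. That would answer a complaint that covariates are missing. It does not answer this one: the article states a rule, and an analysis plan that follows it inherits the defect. Pilot status limits how much the point matters, but the pilot's stated product is effect sizes with intervals, which is where the loss falls.

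Several limits stand:
- The text says balance is checked and factors that differ are included; it names no significance test. The p<0.05 level and the 10 candidates are assumptions used to size the effect. The rule is data-driven under any threshold.
- The correlation is unknown and the final follow-up is 28 weeks after baseline, so the low end of the range is plausible. There the gain is modest.
- The gain from adjusting for sex has not been quantified and may be small.
- Adding covariates to a sparse logistic model carries its own risk, which argues for a short prespecified list.

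A reader might infer more: that the primary abstinence comparison loses a baseline adjustment, that the growth models ignore baseline, or that the rule raises the false-positive rate. The documents and calculations do not support these. Abstinence has no baseline variation, the HIV and anxiety sensitivity growth models very likely contain the baseline wave, and simulated type I error was at or below 5%.

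**Conclusion.** The concern holds in a limited form. The stated rule selects covariates by chance imbalance, has no list or threshold, and in practice excludes the stratification factor. Its measurable cost is lost precision in the between-condition effect sizes of the continuous HIV outcomes. Prespecified baseline adjustment would have about 9%, 22% or 43% lower variance at r = 0.3, 0.5 or 0.7, under the assumptions listed. The rule is inefficient and at most conservative; it does not invalidate the trial. For abstinence the point is one of principle, that covariates should be fixed in advance, and no precision figure attaches to it. The point is worth correcting before analysis because the remedy costs almost nothing.

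**What to change.** Replace the imbalance sentence in Recruitment and Procedures with a prespecified set, and repeat it in Data Analyses:

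- Sex in all between-arm analyses, whatever the observed balance.
- The outcome's own baseline value in the HIV effect-size comparisons. Quality of life has 36 items at baseline and 8 at follow-up (Table 2), so compute the baseline covariate from the 8 items common to both, after confirming that those 8 are among the 36. The AIDS Clinical Trials Group questionnaire goes from 24 to 19 items and needs the same check.
- For abstinence, prespecify any prognostic covariate beyond sex and keep the number to a minimum, since events may be few.
- Report baseline balance descriptively. Keep any adjustment for observed imbalance as a labelled sensitivity analysis.

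The cost is one paragraph, settled before outcomes are examined by arm. No new data are needed: sex is recorded at prescreening and the HIV measures are collected at baseline.
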